## Abstract

**Background:** The reliable assessment, attribution, and alleviation of upper-limb joint stiffness are essential clinical objectives in the early rehabilitation from stroke and other neurological disorders, to prevent the progression of neuromuscular pathology and enable proactive physiotherapy toward functional recovery. However, the current clinical evaluation and treatment of this stiffness (and underlying muscle spasticity) are severely limited by their dependence on subjective evaluation and manual limb mobilization, thus rendering the evaluation imprecise and the treatment insufficiently tailored to the specific pathologies and residual capabilities of individual patients.

**Methods:** To address these needs, the proposed clinical trial will employ the NEUROExos Elbow Module (NEEM), an active robotic exoskeleton, for the passive mobilization and active training of elbow flexion and extension in 60 sub-acute and chronic stroke patients with motor impairments (hemiparesis and/or spasticity) of the right arm. The study protocol is a randomized controlled trial consisting of a 4-week functional rehabilitation program, with both clinical and robotically instrumented assessments to be conducted at baseline and post-treatment. The primary outcome measures will be a set of standard clinical scales for upper limb spasticity and motor function assessment, including the Modified Ashworth Scale and Fugl-Meyer Index, to confirm the safety and evaluate the efficacy of robotic rehabilitation in reducing elbow stiffness and improving function. Secondary outcomes will include biomechanical, muscular activity, and motor performance parameters extracted from instrumented assessments using the NEEM along with synchronous EMG recordings.

**Conclusions:** This randomized controlled trial aims to validate an innovative instrumented methodology for clinical spasticity assessment and functional rehabilitation, relying on the precision and accuracy of an elbow exoskeleton combined with EMG recordings and the expertise of a physiotherapist, thus complementing and maximizing the benefits of both practices.

**Clinical Trial Registration:**
www.ClinicalTrials.gov, identifier NCT04484571.

## Introduction

Stroke is an acute cerebrovascular injury, resulting in numerous cognitive, sensory, and motor deficits among survivors, including complete or partial hemiparesis, loss of strength and dexterity, and/or severe limb rigidity, thus impairing activities of daily living (ADL) and promoting further pathological progression (1, 2). A major contributor to this symptom progression is muscular *spasticity* (3, 4), first defined by Lance (5) as a velocity-dependent hyperactivity of the tonic stretch reflex, causing hyper-resistance to muscle elongation (6). Accordingly, spasticity alleviation has been a primary clinical aim of both pharmacological [e.g., via botulinum toxin (4)] and physical therapies for stroke rehabilitation (7, 8). For the upper limb, robotically assisted training (RAT) has been demonstrated to mitigate spasticity and improve function (9–12), but additional validation remains necessary for incorporation of RAT into official clinical guidelines for post-stroke spasticity (13).

However, the phenomenon of *spasticity* has been inconsistently defined and evaluated in clinical practice to date (14). While several clinical spasticity assessment scales are available (15), none are recommended or used by established consensus (14, 16). On this topic, a recent neurological consensus (14) emphasized that the term “spasticity” should be reserved exclusively for *velocity-dependent stretch hyperreflexia*, distinct from both general hypertonia (involuntary background activation) and mechanical tissue properties. However, current clinical assessment techniques encompass both neurological and non-neurological components in a single measure (6), as true of the most commonly adopted clinical spasticity assessment scale, the Modified Ashworth Scale (MAS). Further, its rater-dependent subjectivity and ordinal quantization render the MAS imprecise, unreliable, and of limited value for the clinical assessment and rehabilitation of post-stroke patients (17–21).

Accordingly, there exists a strong clinical need both for more effective treatments and for more precise and reliable instrumented evaluation methods in characterizing post-stroke joint stiffness, spasticity, and overall motor function, including both biomechanical and neuromuscular properties (14, 22). To this end, numerous robotically instrumented measures have been developed and investigated to evaluate upper-limb spasticity and motor function (22–25) and have demonstrated strong correlation with existing clinical scales (26). Such instrumented measures provide a better understanding of patient pathophysiology, enabling spasticity treatment to be integrated within functional rehabilitation programs specifically designed and adapted to individual patient needs (13, 21). To this end, exoskeletal robotics (27, 28) offer the unique capability both to precisely characterize and assist movements at the level of individual joints.

Based on a previous clinical study demonstrating basic device safety and feasibility in preventing typical increases of post-stroke spasticity (11), the current study protocol describes a randomized controlled trial (RCT) of the NEUROExos Elbow Module (NEEM) (10, 29), a powered elbow exoskeleton, for the treatment and characterization of post-stroke elbow spasticity and motor impairment.

## Materials and Methods

### Objectives

The primary study objective is to rigorously evaluate the efficacy of robotically assisted training as a novel modality for clinical rehabilitation of post-stroke elbow spasticity and motor function, in a randomized controlled trial relative to conventional physical therapy. Secondarily, the study aims to validate a novel instrumented method for elbow stiffness/spasticity evaluation, by combining biomechanical (robotically recorded) and electromyographic (EMG) parameters.

### Study Protocol Design

The present clinical study protocol describes a single-blind randomized controlled trial comparing 4 weeks of RAT using the NEEM robotic elbow exoskeleton to a control group receiving a matched volume of conventional physiotherapy. The primary outcome measures are the Modified Ashworth Scale (MAS) and the upper-extremity Fugl-Meyer Assessment (FMA) scale, two standard clinical scales used to assess upper-limb spasticity and functionality in neurological patients. Subjects are randomly assigned either to the control group (CG), or to the treatment (robotic) group (TG). Both groups will receive a conventional 4-week upper-limb physiotherapy program, consisting of repeated elbow flexion/extension movements: control group patients will focus on manual mobilizations of the limb while aided by the therapist, while the robotic group will receive the same net treatment volume via the robotic device. The treatment group will be further divided into two levels (sub-groups), based on pathological severity: Level 1 corresponds to an FMA score equal or below 28, and Level 2 with FMA >28. The two sub-groups will receive different combinations of robotically assisted *passive* and *active* mobilization treatment modalities, according to their differing clinical needs. Level 1 therapy is designed for patients with very low residual mobility, focusing on *passive mobilization* of the affected limb using a *robot-in-charge* control paradigm (29), where the robot moves the user's arm through a pre-defined spatio-temporal trajectory without requiring his/her active contribution, so as to entrain desired movement patterns and/or reduce joint stiffness (including spasticity). In addition to passive mobilization, Level 1 participants will also perform a limited number of *active mobilization* exercises, using a *patient-in-charge* paradigm (29) in which the user initiates and follows defined movement trajectories, receiving robotic assistance only *as-needed*. According to their higher motor function at baseline, Level 2 subjects will perform a greater proportion of active mobilizations relative to passive exercises (3:1), to emphasize the development of upper limb strength and motor control. Subjects in both treatment sub-groups will also be evaluated for their voluntary movement capacity in each session, via a brief bout of active movements performed with the robotic device in *transparent* (unassisted) mode.

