### Participants and Recruitment

All procedures conform to the Declaration of Helsinki and have been approved by the Ethical Committee for the Azienda USL Toscana Nord Ovest (AUSLTNO) and the Italian Ministry of Health.

The study is conducted at the Recovery and Functional Rehabilitation department of Ospedale Versilia (Lido di Camaiore, Italy), in collaboration with The BioRobotics Institute of Scuola Superiore Sant'Anna. It involves 60 post-stroke patients with right-sided hemiplegia, randomly allocated either to the control (*n* = 30) or treatment (*n* = 30) group. The sample size of each group was calculated based on the hypothesis of a post-treatment MAS score reduction of 0.5 points (compared to pre-treatment, from an average of 2.5 ± 0.70 SD at baseline) with an alpha value of 0.05 and power equal to 80%. (30).

According to inclusion criteria, patients should: (1) be in the age range 18–79; (2) have sustained unilateral hemorrhagic or cerebro-vascular ischemic event in sub-acute (< 6 months) or chronic (> 6 months) phase; (3) experience a functional motor deficit of the right arm (ranging from mild to severe hemiplegia or paresis); (4) have residual cognitive capabilities sufficient for the understanding of basic instructions (Mini-Mental State Examination score > 24); (5) exhibit lack of pain upon passive mobilization of the limb; (6) be able to sign an informed consent. On the contrary, patients are excluded from the study in case of: (1) unstable state of general health; (2) inability to remain in a seated position for a prolonged period (1 h or more); (3) use of a cardiac pacemaker or other active implanted medical devices; (4) passive range of motion (ROM) lower than 10 degrees. In addition, patients who received botulinum toxin injections within 3 months prior to the participation to the study or individuals who follow any additional pharmacological treatment that may alter the outcome of the study are excluded from the participation to the study. Sudden changes in subjects' health conditions, severe alterations in their psychophysical well-being or the inability to attend more than three daily consecutive sessions will lead to the exclusion from the study.

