### Outcome Measures

For the primary objective of the study, patients will be clinically evaluated at the end of the treatment period with the MAS and upper FMA assessment scales, following the same procedure adopted for the initial screening. Score differences between treatment and control group will be statistically analyzed to draw conclusions on the validity and efficacy of conventional and robotic approaches to clinical treatment and assessment practices. These constitute the primary outcome measures of the study.

Regarding the secondary objective, a wide array of biomechanical- and neuromuscular activity-related features will be extracted from the NEEM torque-angle data and from the EMG signals synchronized with the exoskeleton data, respectively.

Biomechanical parameters extracted from the robot in quasi-static exercise include:

Maximum Extension Torque: the maximum torque value recorded during a static hold phase at the maximum extension angle (10);Zero Torque Angle: the angular value corresponding to null torque exerted by the robot; in this configuration, flexor and extensor torques (free of gravity force contributions) are equal and opposite and the system is ideally not applying any force to hold the elbow in position (10);Joint Impedance: measure of the total limb resistance to muscle elongation, computed as the ratio between the difference in joint torque over the corresponding change in joint angular position (33, 34); for constant, slow-speed movements, the main contribution to the joint impedance can be identified in the joint stiffness (i.e., rigidity).EMG signals recorded during quasi-static exercises are used as reference for the background muscle activation, where no spastic contractions should be elicited.

Biomechanical parameters extracted from the robot in passive exercises include Maximum Extension Torque, Zero Torque Angle and Joint Impedance (in this case also including a velocity-dependent viscoelastic component). Additionally, the normalized Torque-Angle Integral is extracted: the integral of the Torque-Angle curve, normalized to the pROM, represents a measure of the expended energy by the robot to move the patient's arm. Higher values correspond to limb stiffening, as the exoskeleton delivers more power to mobilize the limb in the ROM.

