### Statistical Analysis

In addition to descriptive statistics characterizing the study population and the assessment of potential clinical or demographic differences between groups via Pearson's chi-squared test, this study will employ a paired one-way analysis of variance (ANOVA) of all primary outcome measures, with repeated measures taken from baseline (T0) and post-treatment (T1). This series of tests will be contingent on confirmation of the normality of all data distributions using the Shapiro-Wilk normality test. If data are found not to conform to the null hypothesis of Gaussian distribution, then the parametric Mann–Whitney *U*-test (also known as Wilcoxon rank sum test) will be used in place of ANOVA, in pair-wise fashion.

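### Two unranked primary outcomes, sized on MAS alone, with no success rule: if a win on either scale counts at 0.05, familywise error is about 8.4% to 9.8%

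*Protocol article*

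**What the plan says.** Study Protocol Design names two primary outcomes and does not rank them: "The primary outcome measures are the Modified Ashworth Scale (MAS) and the upper-extremity Fugl-Meyer Assessment (FMA) scale". Outcome Measures refers to the same two scales and confirms their status: "These constitute the primary outcome measures of the study". It also says where the conclusions come from: "Score differences between treatment and control group will be statistically analyzed to draw conclusions on the validity and efficacy".

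Statistical Analysis states that "this study will employ a paired one-way analysis of variance (ANOVA) of all primary outcome measures", with a rank-based alternative if normality fails. The scales are therefore tested one by one and not as a composite. That section gives no significance level, no testing order and no allocation of alpha.

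The only alpha in the article is in Participants and Recruitment. There, 30 patients per group follow from the "hypothesis of a post-treatment MAS score reduction of 0.5 points", with baseline 2.5 and SD 0.70, "with an alpha value of 0.05 and power equal to 80" per cent. FMA has no effect size, SD, alpha or power anywhere.

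**The concern.** The primary objective covers both spasticity and motor function, so either scale could be offered as the efficacy result. Unless the rule is fixed in advance, it can be chosen after the results are known. A significant result on one scale could then be reported as success at 5%, although a procedure that accepts either scale has a larger error rate. Conversely, if both scales are required, the stated 80% power is not the power of the primary claim, because it refers to one of the two tests.

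**Working it through.** **Inputs**
- Two primary outcomes (Study Protocol Design, Outcome Measures).
- MAS difference 0.5, SD 0.70, alpha 0.05, power 80%, 30 per group (Participants and Recruitment).
- Assumed because not stated: two-sided tests, 0.05 for each scale, and 0.5 read as a between-group difference. The article words it as a reduction from pre-treatment.
- The correlation between the two test statistics is not given, so a range is shown.

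**1. The plan's own figure.** Normal approximation for two means:

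n per group = 2 × (1.960 + 0.842)² × 0.70² / 0.5² = 30.8, so 31 against the stated 30.

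Power at 30 per group: 0.5 / (0.70 × √(2/30)) = 2.766, and Φ(2.766 − 1.960) = 79.0%. The exact t-test gives 77.6%.

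The stated size is thus reproduced, to within one patient per group, as a MAS-only calculation with the whole 0.05 spent on MAS. The match does not prove the between-group reading. A paired pre-post calculation with uncorrelated visits (SD of change 0.70 × √2 = 0.99) also gives 31, while one with SD of change 0.70 gives 16.

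**2. Error if either scale suffices, each at 0.05.** With uncorrelated statistics: 1 − 0.95² = 0.0975. With correlated statistics the value is 1 − P(|Z₁| < 1.96 and |Z₂| < 1.96) under a bivariate normal:

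| Correlation | Familywise error |
|---|---|
| 0 | 0.0975 |
| 0.3 | 0.0951 |
| 0.5 | 0.0907 |
| 0.7 | 0.0835 |
| 0.9 | 0.0704 |

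Counting only false positives that favour the robot (nominal 0.025), the values are 0.0494 at correlation 0, 0.0454 at 0.5 and 0.0417 at 0.7.

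**3. Error if both must be significant.** At most 0.05, so no inflation. Joint power cannot exceed MAS power (77.6% by exact t). It cannot be computed further, because the article gives no FMA effect or SD.

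**4. Error and power with alpha divided.** At 0.025 per scale, familywise error is at most 1 − 0.975² = 0.0494. MAS power at 30 per group becomes Φ(2.766 − 2.241) = 70.0%, or 67.9% by exact t. Restoring 80% needs 2 × (2.241 + 0.842)² × 0.70² / 0.5² = 37.3, so 38 per group (39 by exact t). Under Holm, MAS can also be rejected at 0.05 once FMA has passed 0.025. Its power therefore lies between 67.9% and 77.6%, depending on FMA.

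**5. Fixed sequence, MAS then FMA.** Familywise error is at most 0.05 and MAS keeps its 77.6%.

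**The case against.** The strongest reply is that the success rule is missing text rather than wrong text, and that it commonly sits in an analysis plan or a full protocol, neither of which is shown. This stands in part: the rule may exist elsewhere. But the article itself commits to the number and rank of the primary outcomes and to the sample size, and no rule fits all of these unchanged. Either scale unadjusted exceeds 5%. Either scale adjusted lowers the stated power. Requiring both leaves the power of the claim unknown. A fixed sequence departs from equal ranking.

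Several stronger readings are tempting and are not supported:
- **That the plan tests both scales at 0.05.** Statistical Analysis gives no level, and 0.05 is attached only to the MAS sizing. Using it for both scales is an assumption.
- **That the false-positive rate is nearly doubled outright.** This needs an either-scale rule, which the article neither states nor excludes. The joint wording of the objective is at least as compatible with requiring both. The top of the range also needs uncorrelated statistics, although both scales are scored on the same arm of the same patients.
- **That pre-post tests within each arm add further chances of success.** The paired wording in Statistical Analysis may suggest this, but Outcome Measures rests the conclusions on differences between groups.
- **That the list of primary outcomes is open.** The Abstract is loose ("The primary outcome measures will be a set of standard clinical scales for upper limb spasticity and motor function assessment, including the Modified Ashworth Scale"), but Study Protocol Design and Outcome Measures close the list at two.

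**Conclusion.** The point holds in conditional form. Two unranked primary outcomes are tested separately, only MAS is sized, and this article does not fix what counts as success. If a win on either scale is accepted and each is tested two-sided at 0.05, familywise error is about 8.4% to 9.8% for correlations from 0.7 to 0, and lower for stronger correlation. If both are required, the error is at most 5% and the problem becomes one of unknown joint power.

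The error range rests on the assumed level, sidedness and correlations. The power figures also rest on reading the 0.5-point change as a between-group difference. The article should be corrected on this point, but it does not show that the trial will make a claim at an inflated error rate.

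**What to change.** State the success rule before unblinding.

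**Preferred:** a fixed sequence. The between-group MAS comparison is tested first at two-sided 0.05, because only MAS is sized. FMA is tested at 0.05 only if MAS is significant. This needs about one sentence each in Outcome Measures and Statistical Analysis, and the equal ranking in Study Protocol Design has to be changed to match. It costs MAS no power. The price is that there is no confirmatory FMA claim if MAS fails, which matters because motor function is part of the primary objective.

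**If both stay primary and either suffices:** use Holm and restate MAS power. At the 0.025 step it is about 68% with 30 per arm, against about 78% at 0.05. Keeping 80% at that step would need 38 to 39 per arm.

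**If both are required:** say so, and say that joint power is not established unless an FMA effect and SD are supplied.

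Under any option, state the significance level and sidedness in Statistical Analysis, say whether the 0.5-point MAS change is a between-group difference or a pre-post change, and align the Abstract with the two scales named in Study Protocol Design.

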### Participants and Recruitment

All procedures conform to the Declaration of Helsinki and have been approved by the Ethical Committee for the Azienda USL Toscana Nord Ovest (AUSLTNO) and the Italian Ministry of Health.

The study is conducted at the Recovery and Functional Rehabilitation department of Ospedale Versilia (Lido di Camaiore, Italy), in collaboration with The BioRobotics Institute of Scuola Superiore Sant'Anna. It involves 60 post-stroke patients with right-sided hemiplegia, randomly allocated either to the control (*n* = 30) or treatment (*n* = 30) group. The sample size of each group was calculated based on the hypothesis of a post-treatment MAS score reduction of 0.5 points (compared to pre-treatment, from an average of 2.5 ± 0.70 SD at baseline) with an alpha value of 0.05 and power equal to 80%. (30).

According to inclusion criteria, patients should: (1) be in the age range 18–79; (2) have sustained unilateral hemorrhagic or cerebro-vascular ischemic event in sub-acute (< 6 months) or chronic (> 6 months) phase; (3) experience a functional motor deficit of the right arm (ranging from mild to severe hemiplegia or paresis); (4) have residual cognitive capabilities sufficient for the understanding of basic instructions (Mini-Mental State Examination score > 24); (5) exhibit lack of pain upon passive mobilization of the limb; (6) be able to sign an informed consent. On the contrary, patients are excluded from the study in case of: (1) unstable state of general health; (2) inability to remain in a seated position for a prolonged period (1 h or more); (3) use of a cardiac pacemaker or other active implanted medical devices; (4) passive range of motion (ROM) lower than 10 degrees. In addition, patients who received botulinum toxin injections within 3 months prior to the participation to the study or individuals who follow any additional pharmacological treatment that may alter the outcome of the study are excluded from the participation to the study. Sudden changes in subjects' health conditions, severe alterations in their psychophysical well-being or the inability to attend more than three daily consecutive sessions will lead to the exclusion from the study.

Patients are recruited from across Tuscany via referral to Versilia Hospital. Once eligibility is confirmed, patients sign an informed consent and are invited for a traditional assessment session with a therapist blinded to their group assignment. Afterwards, patients are randomly allocated to either arm via a random number generator algorithm in blocks of ten. Patients perform daily rehabilitation therapy (5 sessions per week) for 30 min over a 4-week period, for a total of 20 treatment sessions. Subjects assigned to the control group perform 30 min of conventional therapy exercises; patients assigned to the treatment group are subject to 30 min of treatment with the elbow exoskeleton.

Subjects in both groups will undergo both clinical and instrumented evaluations (using the NEEM device) at two time points: pre-treatment (baseline, session T0) and post-treatment (session T1) within 1 week after the end of treatment. Each clinical assessment will include the evaluation of MAS and FMA scores, assessed in blinded fashion. All robotic assessments will include the evaluation of the elbow ROM, as well as other biomechanical and electromyography parameters extracted under different dynamic conditions. Figure 1 represents a scheme of the experimental protocol.

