## Discussion

The current RCT builds on a previous clinical study by Crea et al. (11) that used the NEEM for treatment of post-stroke elbow spasticity in a 2-week (10-session) robotic rehabilitation program, which successfully prevented typical increases in post-stroke spasticity, as measured via MAS and instrumented biomechanical parameters. The present study protocol seeks to further validate the results of the initial single-arm study using a randomized controlled design with a larger sample size over a longer (4-week) treatment period, further incorporating neuromuscular (EMG) activity recordings, new exercise modalities, refined biomechanical parameters, and a personally adaptive study design.

The proposed protocol extends both the previous work and the existing body of clinical literature on robotic upper limb stroke rehabilitation in several important ways. These contributions may be best understood within the framework offered by Duret et al. (40), whose review posited that effective upper limb stroke rehabilitation programs should employ repetitive, intensive, adaptive, and quantifiable therapy. These criteria are echoed in the American Stroke Association's Guidelines on Stroke Rehabilitation (13) and are all fulfilled by the current RCT, with specific focus on the treatment and assessment of elbow spasticity.

To achieve *repetitiveness*, our protocol employs joint trajectories that are first precisely repeated by the robot in a passive mobilization exercise, and then employed as target trajectories for the user to actively follow, with assistance provided *as-needed*. In this way, the delivered highly *intensive* physiotherapy is characterized by more repetitions of higher quality than can be achieved in traditional, manually assisted therapy alone. Indeed, a majority of positive effects in robotic rehabilitation studies to date have been attributed precisely to their ability to administer repetitive, intensive physiotherapy, regardless of modality (13).

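### The 80% power is stated for a pre-to-post MAS fall, so it carries over to robot versus control only if the control arm does not change

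*Protocol article*

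**What the plan says.** Under Participants and Recruitment, the protocol article describes 60 patients "randomly allocated either to the control (*n* = 30) or treatment (*n* = 30) group". It then gives the basis for that number, which rests on the Modified Ashworth Scale (MAS): the figure was "calculated based on the hypothesis of a post-treatment MAS score reduction of 0.5 points (compared to pre-treatment". The parenthesis thus takes the pre-treatment score as the reference point, and the starting level is given as "from an average of 2.5 ± 0.70 SD at baseline". The error rates follow: "with an alpha value of 0.05 and power equal to 80"%. Sidedness is not stated.

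The Objectives section sets the primary question as the efficacy of robotic training "in a randomized controlled trial relative to conventional physical therapy". Study Protocol Design describes the comparator as "a control group receiving a matched volume of conventional physiotherapy", and both arms have 20 sessions of 30 minutes. Outcome Measures says that treatment-versus-control score differences on the MAS and Fugl-Meyer scales will be analysed for the primary objective. Statistical Analysis, however, describes a paired one-way ANOVA on baseline and post-treatment values and names no group factor.

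**The concern.** The effect used for sizing is a fall from baseline within one group. The effect that the trial is meant to estimate is a difference between two randomised groups, both actively treated. The two are equal only when the control group's mean does not move. The article states no expected control-arm change and no between-arm difference, so the reader cannot tell what the randomised comparison is powered for.

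Two misreadings could follow. A significant pre-to-post fall in the robotic arm could be taken as the result that the trial was powered to show, although it is not a randomised comparison. A non-significant difference between arms could be taken as a negative finding at 80% power, when the power for a plausible difference over active therapy may be much lower.

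**Working it through.** **Inputs from Participants and Recruitment:** effect 0.5, SD 0.70 (described as a baseline SD), alpha 0.05, power 80%, 30 per arm.

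**Assumed, because the article does not say:** two-sided test; SD 0.70 for the score analysed; control-arm improvement from 0 to 0.25 points.

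**1. Reproducing the plan's figure.** Two-sample normal formula:

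n per arm = 2 × [SD × (1.960 + 0.842) / difference]² = 2 × [0.70 × 2.802 / 0.5]² = 30.8, so 31.

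Power at 30 per arm: the standard error is 0.70 × √(2/30) = 0.181. Then 0.5 / 0.181 = 2.77, and 2.77 − 1.96 = 0.81, which gives 79.0%. With the t-distribution, n is 31.8 (so 32) and power at 30 is 77.6%. The stated 30 and 80% are therefore reproduced closely if 0.5 is read as a difference between two independent groups with SD 0.70.

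**2. Carrying it to the randomised comparison.** Take a 0.5-point fall in the robotic arm and let the control arm fall by c. The between-arm difference is 0.5 − c.

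| Control-arm fall c (assumed) | Between-arm difference | Power at 30 per arm, t-test | Power, normal formula | n per arm for 80%, normal formula |
|---|---|---|---|---|
| 0 | 0.50 | 77.6% | 79.0% | 31 |
| 0.10 | 0.40 | 58.6% | 60.0% | 49 |
| 0.20 | 0.30 | 37.2% | 38.2% | 86 |
| 0.25 | 0.25 | 27.5% | 28.2% | 124 |

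**3. What 30 per arm can detect.** At two-sided 5%, 80% power and SD 0.70, the detectable between-arm difference is 0.181 × 2.802 = 0.51 by the normal formula, and 0.515 (about 0.52) by the t-test.

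**4. Dependence on the SD.** If the analysed score is the change from baseline, its SD is 0.70 × √[2(1 − r)], where r is the pre-post correlation. This equals 0.70 only at r = 0.5. At r = 0 it is 0.99, and power for a difference of 0.5 falls to about 50% (normal formula). If the post-treatment score is instead adjusted for baseline, the SD is 0.70 × √(1 − r²). At an assumed r of 0.5 this is 0.606, and the detectable difference becomes 0.515 × 0.866 = 0.446, about 0.45. The article gives no value for r.

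**The case against.** The best defence is that the number is sound and only its description is loose. The two-sample formula returns 31 per arm, and 30 per arm give 78–79% for a between-arm difference of 0.5. The authors may have meant exactly that and worded it as pre-to-post. This stands as far as the number goes: n = 60 is not shown to be wrong. It does not rescue the sentence, which names the pre-treatment score as the reference and leaves the change under active control unstated.

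Stronger readings are tempting, and the document does not support them:

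- **That 30 per arm is too few.** This would need a known control-arm improvement, and none is given. The lower powers in the table rest on assumed values.
- **That 30 cannot come from the pre-post hypothesis.** A reader might note that a paired t-test with SD of change 0.70 needs only 18 patients, and infer that pre and post scores were treated as independent samples. But 0.70 is given as the baseline SD; using it as the SD of change assumes r = 0.5. At r = 0.1 the SD of change is 0.94 and a paired t-test needs 29.7, so 30. The formula used cannot be identified.
- **That the earlier device study contradicts a 0.5-point fall.** The Discussion says of it, "which successfully prevented typical increases in post-stroke spasticity". It was a single-arm, 2-week programme, and the sample-size sentence cites a different reference.
- **That losses were ignored.** A condensed article may leave an attrition allowance to the full protocol. Any loss rate used here would be an assumption.

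**Conclusion.** The point holds as a mismatch between the sample-size hypothesis and the primary comparison. The published 80% is not a property of robot versus control unless the between-arm difference is 0.5 with SD 0.70, which requires an unchanged control arm. On that condition the design has 78–79%. For assumed control improvements of 0.1 to 0.25 points, power at 30 per arm runs from about 59% down to about 27%.

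These figures assume a two-sided 5% test, SD 0.70 for the analysed score, and all 30 per arm evaluable. The conclusion that the statement refers to the wrong contrast depends on none of them.

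**What to change.** Keep n = 60. Replace the pre-post hypothesis with a between-arm statement, for example: *30 evaluable patients per arm give 80% power at two-sided 5% to detect a between-arm difference in MAS of about 0.52 points (SD 0.70 assumed for the analysed score).* State the control-arm change that is assumed, and label any loss rate as an assumption.

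If the Statistical Analysis section is changed to a between-arm comparison of post-treatment MAS adjusted for baseline, the detectable difference can be given as about 0.45, with the assumed correlation of 0.5 stated. The section plans no such adjustment now, so that figure should not be quoted unless it is changed.

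The cost is rewording: no extra patients and no change in conduct. The price is that the sponsor must commit to a between-arm difference and say why one of that size matters over conventional therapy.
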